## Methods

### Study design

The efficacy of CBT for loneliness in children and young people will be evaluated through a randomised multiple-baseline single-case experimental design (SCED) [28–30]. The design consists of AB+ post-intervention, where A is the baseline phase, B is the intervention phase and then a post-intervention phase. In the SCED approach participants are repeatedly assessed on at least one independent variable, in this case self-reported loneliness on the Three-item Loneliness Scale [34], across each phase of the intervention. This repeated measurement and within subject replication is then used to test the effects of the intervention for individual participants [28, 30]. Multiple-baseline SCEDs are a controlled experimental approach, with multiple-baselines protecting against threats to internal validity [40].

The construction of this SCED trial and the reporting of the results will be in accordance with the Single-Case Reporting Guidelines in Behavioural Intervention (SCRIBE) [30].

The study has received ethical approval from Royal Holloway, University of London on 22.03.2021 (ethical approval number: 2489). The study was registered with ClinicalTrials.gov on 07.12.2021 (registration number: NCT05149963).

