**Fig 1 pone.0278746.g001:**
[figure not shown]
Showing the trials schedule of enrolment, interventions and assessments.

Participants will be recruited via advertisements emailed to schools, shared via social media and word of mouth. Participants and their parents/carers will be sent an electronic information sheet and given the opportunity to ask any questions before completing an online consent form. Participants will provide informed ascent as they are under 18, with parents/carers providing informed consent. Participants and their parents/carers will then complete a baseline eligibility assessment. They will complete a range of online questionnaires via Qualtrics [41], a secure online platform. They will then attend a remote research assessment appointment to determine whether the family meet the eligibility criteria. The researcher completing the baseline and post-intervention assessments will not be involved in the clinical intervention and will be blinded to baseline allocation. After all baseline assessments for the participant group are completed, they will be discussed within supervision to confirm that the participants meet eligibility criteria. Eligible participants will then be randomised using a random number generator to one of four different baseline lengths (12 days, 19 days, 26 days or 33 days [42]. The decision to have a minimum of 12 observations per phase meets the requirements for guidelines and standards [43] and will allow for sufficient power for Tau-U analysis [44, 45].

Each of the families will then be contacted to inform them of their allocation. Randomisation and contacting of the families will be completed by a third researcher, who is not involved in either the clinical intervention or research assessments. Families will receive a £25 voucher for completing the baseline eligibility assessment. A letter will also be sent to their General Practitioner (GP) informing them of the family’s participation in the research study. The setting for the entire study will be remote via Zoom [46], with participants recruited from across the United Kingdom (UK).

All participants in the group will begin their baseline phase concurrently. During the baseline phase participants will be asked to complete the Three-Item Loneliness Scale [34] each day via Qualtrics [41]. SMS message reminders will also be sent to the young people and their parent/carers each day.

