### Data analysis

#### Primary outcome measure

The primary outcome measure of the SCED (self-reported scores on the Three Item Loneliness Scale [34]) will be analysed using visual inspection and statistical analysis.

For visual analysis, in accordance with SCED procedure, each participants data will be graphically represented on a line graph for the outcome variable [65, 66]. The baseline phase will be examined to determine a stable control. Data within and between each phase will then be compared for a) change in trend or symptom severity across phases, b) the degree of the slope on the graph which indicates the strength of the trend and c) change in the variability of the data to indicate stability in symptom change. Data will be mapped and inspected using both within-phase (evaluation of data patterns across participants in a single phase) and between-phase (comparison across adjacent phases for each participant) analyses [65, 66].

For statistical analysis Tau-U [45] will be used, which is a test specifically designed for single case research and has been used in previous SCEDs of psychological interventions [67, 68]. It is not dependent on distribution assumptions and calculations are based upon consideration of all data points. A further strength of the approach is that it can control for unwanted trends or variability in baseline scores to identify whether any change is the result of the introduction of the intervention [45]; making it a robust approach for SCED analysis. Tau-U will be used to analyse the overlap between the baseline and intervention phase and the baseline and post-intervention phase. The statistical analysis can be understood as the percentage of data that ‘improves’ across the phases of the study whilst considering any pre-existing baseline trends [68]. Tau-U will also be used to calculate an effect size and weighted average across all cases for the primary outcome variable.

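### Tau-U compares each participant only with themselves, so it cannot show that CBT caused a change, and no planned comparison uses the staggered concurrent baselines as a control

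*Protocol article*

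**What the plan says.** Study design rests the causal claim on the staggered baselines: "Multiple-baseline SCEDs are a controlled experimental approach, with multiple-baselines protecting against threats to internal validity". Under Procedure, participants are randomised to 12, 19, 26 or 33 baseline days, and "All participants in the group will begin their baseline phase concurrently".

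The Primary outcome measure part of Data analysis then defines the comparisons:

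- Statistical: "Tau-U will be used to analyse the overlap between the baseline and intervention phase and the baseline and post-intervention phase". Tau-U is also used to "calculate an effect size and weighted average across all cases for the primary outcome variable".
- Visual: "within-phase (evaluation of data patterns across participants in a single phase) and between-phase (comparison across adjacent phases for each participant) analyses".
- Interpretation, given as a strength of Tau-U: "it can control for unwanted trends or variability in baseline scores to identify whether any change is the result of the introduction of the intervention".

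Shared outside events are otherwise handled by a questionnaire on COVID-19 and other events, given at the post-intervention assessment and reported with the feasibility results.

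**The concern.** Baselines that start together and end at different times protect against outside events in one way. When some participants start treatment, others are still untreated on the same dates. If scores fall only in those who have started, an outside event is an unlikely explanation. If everyone's scores fall, treatment is an unlikely one.

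None of the planned comparisons looks at this. Trend control does not fill the gap, because it sees only movement that has begun inside that person's own baseline. A school holiday, a new term, a change in COVID-19 restrictions or habituation to repeated ratings could move the whole group after the shorter baselines have ended. Averaging over cases then makes the result look more certain, because the shared change does not average out.

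Efficacy is the primary objective, and the introduction criticises earlier work for lacking controlled designs. A causal statement resting on Tau-U alone would be open to the same criticism.

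**Working it through.** **1. What each comparison contrasts**

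| Planned comparison | Participants | Phases | Treated against untreated on the same dates? |
|---|---|---|---|
| Tau-U | one | baseline against intervention or post-intervention | no |
| Weighted average | all, pooled after the within-person step | as above | no |
| Visual, within-phase | several | one | no |
| Visual, between-phase | one | adjacent | no |

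**2. Where concurrent control exists**

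Intervention starts on days 13, 20, 27 and 34. Treated and untreated participants coexist only on days 13-33 (21 days). Those starting on day 34 have no concurrent control.

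**3. Effect of a shared change on Tau-U**

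The protocol gives no error rate, effect size or shared-change size for Tau-U, so there is no figure to reproduce. Assumptions:

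- No treatment effect, independent errors, and a shared drop of 0.5 SD from day 22.
- Baseline lengths of two each (n=8) or 12, 19, 26, 33, 12, 33 (n=6).
- Twelve session readings, at 1, 4, 8, 11, 18, 25, 32, 39, 53, 67, 81 and 95 days after baseline ends. This follows Procedure, taking bi-weekly as twice weekly.
- Significance for improvement means z beyond 1.96 in that direction (nominal 2.5%).

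Formulas: Tau = S_AB/(nA nB). Trend-corrected Tau-U = (S_AB - S_A)/(nA nB). Variance v = (nA + nB + 1)/(3 nA nB). Pooling is by inverse variance.

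For a pair of readings on either side of the drop, the expected net sign is 2Φ(0.5/√2) - 1 = 0.276 towards improvement.

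| Baseline | Baseline days before drop | Session readings after drop | Tau, uncorrected | Removed by trend correction | Tau-U, corrected | 1/v |
|---|---|---|---|---|---|---|
| 12 | 12 of 12 | 9 of 12 | 9/12 × 0.276 = 0.207 | 0 | 0.207 | 17.28 |
| 19 | 19 of 19 | 11 of 12 | 11/12 × 0.276 = 0.253 | 0 | 0.253 | 21.38 |
| 26 | 21 of 26 | 12 of 12 | 21/26 × 0.276 = 0.223 | (21×5)/(26×12) × 0.276 = 0.093 | 0.130 | 24.00 |
| 33 | 21 of 33 | 12 of 12 | 21/33 × 0.276 = 0.176 | (21×12)/(33×12) × 0.276 = 0.176 | 0 | 25.83 |

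The correction removes the whole artefact in the 33-day baseline, part of it in the 26-day baseline, and none in the 12- and 19-day baselines, which ended before the drop.

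- n=8: sum of 1/v = 176.97, SE 0.075, pooled corrected value 0.137, z = 1.82. Chance of a false positive: Φ(1.82 - 1.96), about 44-45%.
- n=6: sum of 1/v = 131.59, SE 0.087, pooled corrected value 0.119, z = 1.37. Chance: Φ(1.37 - 1.96), about 28%.

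Simulation with integer 0-12 scores agrees:

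| Shared change, no treatment effect | Trend-corrected, n=6 | Trend-corrected, n=8 |
|---|---|---|
| None | about 4-5% | about 4-5% |
| 0.5 SD drop on day 22 | 26-30% | 42-44% |
| Drift of 0.5 SD per 100 days | 23-25% | 28-30% |

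The exact reading days move these rates by a few points. The corrected statistic already rejects in about 4-5% with no shared change, so that is the reference, not 2.5%.

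**4. What a calendar-adjusted model could use**

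Session readings by day 33, at two per week for two weeks and then one per week:

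- 12-day baseline: 21 days, 2 + 2 + 1 = 5.
- 19-day: 14 days, 2 + 2 = 4.
- 26-day: 7 days, 2.
- 33-day: 0.

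Readings are due before each session, and the first two sessions are assessment and formulation. Reading 4 is therefore the first that can follow an active module. That leaves 2 + 1 + 0 + 0 = 3 of 11 readings per set of four participants. In simulation, power for a 0.8 SD effect is roughly 66-82% if the full effect is present at reading 1, and about 7-9% if it starts at reading 4.

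**The case against.** A reader might infer that every shared change will be credited to CBT. The documents do not support that. Trend control removes part of a shared change that falls inside a person's baseline, as the 26- and 33-day rows show. Each baseline is inspected for stability, and the within-phase visual comparison looks across participants, so movement in untreated participants could be noticed. Families are asked about outside events, and Limitations urges caution and speaks of preliminary evidence. These points narrow the concern. They do not make any planned comparison a concurrent control, and the false-positive rates above remain after trend correction.

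A reader might also infer that a model with calendar terms would solve the problem and should decide whether causal wording is allowed. It would not. On days 1-33 it rests on few readings, most of them before any active module, and would usually miss an effect that begins with those modules. It is unaffected by events from day 34 only because it drops all later readings. Such events lie beyond what any use of the stagger can address, so they are no argument that the stagger was left unused.

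It may be said that an article condenses the full plan. That would excuse a missing detail. Here the section defines the visual comparisons and makes the causal statement itself.

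**Conclusion.** The concern holds in this limited form. The sentence that lets Tau-U identify cause is wrong, and the protection claimed for concurrent randomised baselines is not used by any comparison the protocol defines. The baseline-against-intervention contrast can therefore credit CBT with a shared change that is not already a trend in the person's own baseline.

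Under the assumed shared changes, the trend-corrected pooled result is falsely significant in roughly a quarter of trials with 6 participants and 28-44% with 8. These rates depend on the assumed shared change, the reading days, the allocation and independent errors. None of these sizes is in the documents. The direction does not depend on them. After day 33, which includes the whole post-intervention phase, no analysis of this design can separate a shared change from an effect of CBT.

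**What to change.** 1. Reword the Tau-U sentence under Primary outcome measure. Describe Tau-U as a within-person before-after effect size adjusted for that person's baseline trend, and remove the claim that it identifies the cause of change.
2. Add to the visual analysis a stacked graph of all participants on a common calendar axis. At each start date, judge whether scores change in those starting CBT while those still in baseline stay level. State that this control exists only on days 13-33, so it is available for the starts on days 13, 20 and 27 but not day 34.
3. Optionally, report an estimate from days 1-33 with terms for participant, calendar week and phase, as a supporting analysis only. State that it rests on at most 5, 4, 2 and 0 session readings for the four baseline lengths (bi-weekly taken as twice weekly). State also that its power is under 10% for 0.8 SD if the effect begins with the active modules, so a null result is not evidence against CBT.

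Items 1 and 2 cost a change of wording and one graph from data already planned. Item 3 needs no new data either. Its cost is the risk of misreading a weak estimate, which the stated limits are meant to prevent.

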#### Secondary outcome measures

It will be assessed how many of the participants display a reliable and clinically significant change [38] in total loneliness scores on the UCLA-LS-3 [35] and parent and self-reported impact scores on the SDQ [36]. It will also be examined how many participants display reliable change [38] in parent and self-reported Total Anxiety and Depression Scores on the RCADS [37], as well as how many participants report ‘clinically significant’ and ‘borderline clinical’ scores at baseline and post-intervention.

For the UCLA-LS-3 criterion B will be used to determine clinically significant change [38]. For criterion B, the participant must move within 2 standard deviations of the mean of a non-clinical comparison population. Criterion A and C will not be used due to lack of normative data available for a ‘clinically lonely’ population. The test-retest reliability used for the calculation will be 0.73 [35]. Normative data for the comparison population will be taken from a large-scale adolescent community sample, mean = 32.82, SD = 9.43 [49]. Reliable change will be calculated using Jacobson and Truax [38], whereby the baseline mean is subtracted from the post-intervention mean then divided by the standard error of measurement, giving the Reliable Change Index (RCI). The RCI indicates what would be categorised as clinically reliable improvement or deterioration.

For the RCADS well-defined norms are available [37], with raw scores being converted to age and gender-specific T-scores. A T-score of 65 means the young person is scoring in the top 7% for un-referred young people and is classified as “borderline clinical”. A T-score of 70 means that the young person is in the top 2% of unreferred young people and is described as the “clinical” threshold. The number of participants scoring within the clinical, borderline clinical and non-clinical ranges at baseline and post-intervention will be reported. As this current study has a small sample, the Reliable Change Index (RCI) used will be from a large normative sample [37].

For the SDQ parent and self-reported impact scores criterion C will be used to calculate clinically significant change. For criterion C, the participant’s score must move to the comparison side of the point halfway between the clinical and comparison group mean. Criterion C will be calculated as both clinical and comparisons norms are available. A test-retest reliability of .71 will be used [69]. For parent-report M = 0.4, SD = 1.1 will be used for comparison norms [36] and M = 6.2, SD = 2.7 for clinical norms [70]. For child report M = 0.2, SD = 2.8 will be used for comparison norms [36] and M = 5, SD = 3.3 [70] for clinical norms. For the SDQ impact scores, the Reliable Change Index (RCI) values will be based on those reported by Goodman [36] from a large normative sample.

The VAS and GBO’s will also be visually presented and the means and standard deviations of scores at baseline and post-intervention will be reported.

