## Abstract

Loneliness is a significant problem for young people and is associated with a range of physical and mental health difficulties. Meta-analyses have identified that interventions aimed at young people who report loneliness as their primary problem are lacking within the literature. In adults, the most effective interventions for loneliness are those which target the underlying maladaptive social cognitions. Therefore, we have developed a modular Cognitive Behavioural Therapy (CBT) intervention for children and young people. The aim of this study is to conduct a multiple baseline single-case experimental design (SCED) to assess the efficacy, feasibility and acceptability of this intervention. In total 6–8 11–18-year-olds and their families will be recruited. The design consists of AB+ post-intervention, where A is the baseline phase, B is the intervention phase and then a post-intervention phase. Participants will complete a baseline assessment, before being randomised to one of four different baseline lengths (12 days, 19 days, 26 days or 33 days). Participants will then complete an average of 12 sessions of CBT, with the aim being to reduce their feelings of loneliness. Participants will then complete a 12-day post-intervention phase. Participant loneliness will be repeatedly assessed throughout the three phases of the intervention using the Three-item Loneliness Scale, which will be the primary outcome. Secondary outcomes will be reliable and clinically meaningful change on the UCLA Loneliness Scale, Revised Child Anxiety and Depression Scale (RCADS) and Strengths and Difficulties Questionnaire (SDQ). Feasibility and participant satisfaction will also be assessed and reported.

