### Aims and objectives

The primary objective will be to evaluate the efficacy of CBT for loneliness in children and young people ages 11–18. The primary outcome will be differences in scores on the Three-Item Loneliness Scale [34] between baseline and intervention and baseline and post-intervention. It is hypothesised that there will be a significant decrease in self-reported loneliness across both time-points. The secondary outcomes will be self-reported loneliness scores on the UCLA Loneliness Scale (UCLA-LS-3) [35] and self and parent-reported scores on the Strengths and Difficulties Questionnaires (SDQ) [36] and Revised Child Anxiety and Depression Scale (RCADS) [37]. It is hypothesised that there will be a reliable and clinically meaningful change [38] in total loneliness scores on the UCLA-LS-3, in the impact scores on the SDQ and in total anxiety and depression scores on the RCADS.

The secondary objective is to evaluate the feasibly and acceptability of the intervention process. This will be defined in terms of a) meeting the recruitment target, b) participant retention and c) participant feedback of the intervention using the Experience of Service Questionnaire [39].

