## Discussion

To the best of our knowledge this will be the first study to test a CBT-based intervention for loneliness in young people ages 11–18. The intervention is modular and based upon Käll et al., [23] cognitive behavioural analysis of chronic loneliness. The intervention incorporates translated elements of Käll et al., [55] online intervention, and is informed by MATCH-ADTC [50], Groups4Health [51], PEERS social skills training [52] and CBT for Social Anxiety Disorder for adolescence [53]. The intervention will be evaluated through a SCED [28–30] of 6–8 participants. The primary objective of this study will be to test the efficacy of the intervention in terms of whether there are differences in scores on the Three-Item Loneliness Scale [34] between the different phases. The secondary objectives will be to examine whether there is reliable and clinically meaningful change [38] in self-reported loneliness scores on the UCLA-LS-3 [35], self and parent-reported impact scores on the SDQ [36] and self and parent-reported total scores on the RCADS [37]. The third objective will be to evaluate the feasibly and acceptability of the intervention. This will be defined in terms of a) meeting the recruitment target, b) participant retention and c) participant feedback of the intervention using the Experience of Service Questionnaire [39]. The results of the trial will be published in a peer reviewed journal and presented at relevant conferences.

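### The RCADS secondary outcome is stated as reliable and clinically meaningful change, but the planned analysis reports the two parts separately and never derives the joint outcome

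*Protocol article*

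**What the plan says.** The outcome is stated three times, each time with the same standard for all three instruments.

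- Abstract: "Secondary outcomes will be reliable and clinically meaningful change on the UCLA Loneliness Scale, Revised Child Anxiety and Depression Scale (RCADS"), with the SDQ completing the list.
- Aims and objectives: the hypothesis opens "It is hypothesised that there will be a reliable and clinically meaningful change [38] in total loneliness scores on the UCLA-LS-3" and continues "in the impact scores on the SDQ and in total anxiety and depression scores on the RCADS".
- Discussion: the objective is repeated for the UCLA-LS-3, the SDQ impact score and the RCADS total, in one sentence.

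The analysis text under Secondary outcome measures then separates the instruments. For the UCLA-LS-3 and the SDQ impact score the combined event is counted: "It will be assessed how many of the participants display a reliable and clinically significant change [38] in total loneliness scores on the UCLA-LS-3" and likewise for the SDQ. Criterion B (UCLA-LS-3) and criterion C (SDQ) make this operational. For the RCADS there are two separate products. The first is "It will also be examined how many participants display reliable change [38] in parent and self-reported Total Anxiety and Depression Scores on the RCADS". The second is "The number of participants scoring within the clinical, borderline clinical and non-clinical ranges at baseline and post-intervention will be reported". The range boundaries are T 65 (borderline) and T 70 (clinical). The reliable change index is to come from a cited normative sample, and its value is not printed.

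**The concern.** Reliable and clinically meaningful change is a property of one participant: the score moves by more than measurement error, and the same participant's clinical status changes. The RCADS plan counts the first condition alone and reports the second only as group totals before and after. It gives no rule that joins them within a person and no reason for treating the RCADS differently.

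Two things are at stake. The RCADS part of the hypothesis cannot be judged from the planned output. And the only within-person RCADS count is more lenient than the rule for the other two instruments, so a reader who sets it beside the stated hypothesis may credit the intervention with more than was shown. If the joining rule is chosen after the scores are known, with 6–8 participants, that choice can settle the result.

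This is not detail left to a fuller document. The article specifies an RCADS analysis, and it differs from the outcome that the article states.

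**Working it through.** **1. The plan's own figures.** The only RCADS numbers given are the tail shares at the two thresholds, for example "A T-score of 65 means the young person is scoring in the top 7% for un-referred young people". On the conventional T scale (mean 50, SD 10; assumed, not stated in the article) the upper tail is 1 − Φ((T − 50)/10):

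- T 65: 1 − Φ(1.5) = 6.68%, stated as 7%.
- T 70: 1 − Φ(2.0) = 2.28%, stated as 2%.

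Both reproduce, so the thresholds are usable as printed.

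**2. Can the planned summaries yield the joint count?** Take 8 participants (upper end of the recruitment aim), 4 at or above T 65 at baseline, 2 afterwards, and 3 reliable improvers. Two data sets fit these totals:

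- Two participants slip below 65 by a few points, within error, and the three reliable improvers all started below 65. Joint count 0.
- Three of the four fall reliably to below 65, and one who started below 65 rises to 65 or above. After treatment 1 + 1 = 2 are at or above 65. Joint count 3.

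Enumerating every arrangement:

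| At or above 65, baseline | At or above 65, post | Reliable improvers | Possible joint counts |
|---|---|---|---|
| 4 | 2 | 3 | 0, 1, 2, 3 |
| 2 | 1 | 3 | 0, 1, 2 |
| 6 | 3 | 4 | 0, 1, 2, 3, 4 |
| 0 | 0 | 3 | 0 |

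This step needs no assumption about reliability or effect size.

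**3. Direction.** Everyone who meets the joint rule also shows reliable change. So the reliable-change count is at least as large as the joint count. The two can be equal (3 of 3 in the first row).

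**4. Illustrative size.** The article gives no RCADS reliability, index, baseline mean or expected change, so all of these are assumed. With SD 10, index = 1.96 × 10 × √(2(1 − r)):

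- r = 0.75: 19.6 × √0.50 = 13.9 T points
- r = 0.80: 19.6 × √0.40 = 12.4
- r = 0.90: 19.6 × √0.20 = 8.8

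Simulated pairs: true T normal with between-person SD 8, error SD 10√(1 − r), true fall of 10 points, joint rule = reliable decrease plus a move from ≥ 65 to < 65. At baseline mean T 70:

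| r | Reliable decrease | Joint rule met | Reliable changers not meeting the joint rule | of which started below 65 |
|---|---|---|---|---|
| 0.75 | 29% | 20% | 31% | 15 points |
| 0.80 | 35% | 23% | 34% | 17 points |
| 0.90 | 61% | 34% | 45% | 22 points |

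At mean 60, 55–69% of reliable changers miss the joint rule, and 54–67% of them started below 65. At mean 75, 32–43% of reliable changers are still at or above 65 afterwards.

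As expected counts among 8 participants (r = 0.85, fall of 10 points, true-score SD 10√r), 3.6 show reliable change. Of these 0.3, 1.3 or 2.0 meet the joint rule at baseline means of 50, 60 and 70.

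**The case against.** A reader might infer that the plan over-counts RCADS responders. The article does not support that. It defines no RCADS responder, labels the count as reliable change, which is what it measures, and uses a different label for the UCLA-LS-3 and SDQ. Nothing in it says that the RCADS count will be presented as the joint outcome. This objection stands in full.

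Clinical status is also not ignored. Two thresholds are named and range totals are promised, so one could read reliable change and clinical range as the two components of the outcome for this measure. That is a fair reading of clinically meaningful in isolation. But the Aims cite the same reliable-change reference for all three instruments in one sentence, and the article never says how the components combine.

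There is a plausible reason for separate treatment. Eligibility sets a UCLA-LS-3 cut-off but no minimum RCADS score, and it requires that current difficulties are not attributable to a significant mental health problem. Some participants may therefore start below T 65 and could never cross it. The article does not give this reason, but it limits what the simulation shows. At mean T 70, half of the apparent shortfall consists of such participants, who are not false improvers.

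Finally, with 6–8 participants and anonymised data to be deposited, the joint count could be made later from individual scores. That is true of the data, but not of the planned summaries, and the rule would then be chosen with the results in view.

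**Conclusion.** The mismatch is real and internal to the article. Three sections state a joint RCADS outcome; the analysis section derives only its parts, and separate range totals cannot put them together. That conclusion rests on the text and on the enumeration, not on any assumed value.

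Over-statement is possible, not established. It arises only if the reliable-change count is read against the hypothesis in the Aims. Its direction is fixed, since it can never understate, but its size cannot be found from the article and may be zero. The 31–45% at mean T 70 depends on assumed reliability, spread, baseline and effect, and on T 65 as the cut-off. It should not be quoted as an estimate for this trial.

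This is one secondary measure in a small single-case series. It merits correction before data are seen, but it does not touch the primary analysis.

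**What to change.** Either of two changes removes the contradiction.

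**Option 1: derive the stated outcome.** Under Secondary outcome measures, for self-report and parent-report separately:

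- Count participants with a reliable decrease who also move from at or above T 65 at baseline to below 65 post-intervention. Report T 70 in the same way.
- Use as denominator those at or above the threshold at baseline, and state how many started below it.
- Replace the two sets of range totals with a paired baseline-to-post table of clinical, borderline and non-clinical status.
- Keep the reliable-change count as a separately labelled figure.

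**Option 2: match the claim to the analysis.** Reword the Abstract, Aims and objectives and Discussion so that, for the RCADS, only reliable change is claimed, with range totals as description.

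Option 1 costs a few sentences and one small table, with no new data. Its drawback is a smaller joint count on a smaller denominator, possibly very small if most participants start below T 65. Option 2 costs only wording, but gives up the clinical part of the RCADS hypothesis.
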